#### Hematological Toxicities

Hematological toxicity will be monitored in accordance with following time points

Cycle 1: Complete hemogram for monitoring of toxicity will be done on D8 ( D7-D10)

Subsequent Cycles : Complete hemogram for monitoring of toxicity will be done at start of each cycle.

Since hematological toxicities is caused by methotrexate , dose modifications should be done for both agents according to dose levels defined in Table 6 for the most severe haematological toxicity.

The doses used for subsequent cycles in case of hematological toxicity are

|                                                        | Methotrexate | Celecoxib | Erlotinib |
|--------------------------------------------------------|--------------|-----------|-----------|
| ANC > 1 (X10  /L) and Platelet > 50,000    | 100% dose    | 100% dose | 100% dose |
| ANC < 1 (X10  /L) and/or Platelet < 50,000 | 75% dose     | 100% dose | 100% dose |

Table 4: Table showing dose modifications with hematological toxicities experienced.

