| Scientific Title               | “Stage I/II study of oral metronomic methotrexate with celecoxib and erlotinib as palliative chemotherapy in oral cancer patients”                                                                                                                                                                                                                                                                                                           |
| Countries of Recruitment       | India                                                                                                                                                                                                                                                                                                                                                                                                                                               |
| Health Condition Studied       | Squamous cell cancers of head and neck region warranting palliative chemotherapy                                                                                                                                                                                                                                                                                                                                                                    |
| Interventions                  | Weekly oral chemotherapy with:
De escalating dose of oral methotrexate given weekly D1 
 
1. Dose Level 0: 15 mg/m^2
 
2. Dose Level I: 12 mg/m^2
 
3. Dose Level II: 09 mg/m^2
 
4. Dose Level III: 06 mg/m^2
 
5. Dose Level IV: 03 mg/m^2
 
 Fixed dose of erlotinib 150 mg OD
Fixed dose of celecoxib 200 mg BD |
| Aim                            | Stage 1 : To identify the optimal biological effective dose (OBD) of methotrexate in combination with celecoxib ( 200 mg PO BD) and erlotinib (150 mg PO OD)

Stage 2 : To estimate the median PFS in head and neck cancer patients warranting palliative chemotherapy with the combination of celecoxib 200 mg BD, erlotinib 150 mg OD and oral weekly methotrexate                                                                          |

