**In stage 1 : The dose of methotrexate will be according to the dose level**

**In stage 2 : The dose of methotrexate will be the dose selected from stage 1**

All chemotherapy medications will be taken 1 hour before breakfast. The methotrexate is available in 2.5 mg tablets. Hence the dose of methotrexate will be rounded off to the nearest lower numerical which is a multiple of 2.5. This could enable delivery of methotrexate without the need for breaking or crushing the tablets. All methotrexate tablets will be taken together.

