### 11.4 Toxicities and Dosing Delays / Dose Modifications

All patients will be evaluable for adverse events due to chemotherapy during the study. The schedule for monitoring of adverse events is mentioned under the time and events table. All toxicities will be evaluated as per the NCI CTCAE 4.03 criteria. The final dose modification according to the following tables should be based upon the worst grade of adverse event experienced. If any of the treatment agents is held or discontinued for toxicity or intolerance, further protocol directed treatment will be stopped. Held doses of any agent will not be made up at a later date. If more than one dose reduction applies, then use the most stringent (i.e., the greatest dose reduction). Doses that are reduced at any point during a cycle will not be re-escalated. Grade I toxicities will not result in dose modifications. Patients will be removed from the protocol in the event of discontinuation of any of the agents mentioned in the protocol as per criteria mentioned below.

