**Non Hematological Toxicity**

MCT has very limited non hematological side effects. The subsequent subsections show the dose modifications that should be done for derangements of metabolic parameters and non hematological toxicity during the treatment.

Nausea & Vomiting

Nausea and vomiting are unlikely. Primary prophylaxis against nausea and vomiting is not required as per the schedule mentioned in Treatment schedule above. Patients with Grade III – IV nausea and vomiting should have the dose withheld till the nausea, vomiting subsides to Grade I or less. Patients who have had one episode of Grade III / IV nausea or vomiting should have primary prophylaxis with addition of ondansetron (4 mg BD ) from the subsequent cycles of methotrexate chemotherapy. If patients continue to have Grade III- IV vomiting despite instituting antiemetic ondansetron then from the subsequent cycles of methotrexate chemotherapy additive antiemetics can be added. If in spite of high risk antiemetic prophylaxis patients continue to have vomiting ( Grade III-IV) then methotrexate should be discontinued.

Nephrotoxicity

Nephrotoxicity will be monitored in accordance with following time points

Cycle 1: Renal function test ( inclusive of serum urea, creatinine ,Na and K) for monitoring of toxicity will be done on D8 ( D7-D10)

Subsequent Cycles : Renal function test ( inclusive of serum urea, creatinine ,Na and K) for monitoring of toxicity will be done at start of each cycle.

The dose reduction in case of nephrotoxicity will be done in accordance with below mentioned table.

| Serum creatinine clearance | Methotrexate | Celecoxib  | Erlotinib          |
|----------------------------|--------------|------------|--------------------|
| > 30 ml/min                | 100 % dose   | 100 % dose | No dose adjustment |
| 15-30 ml/min               | 50% dose     | Avoid      | No dose adjustment |
| < 15 ml/min                | Avoid        | Avoid      | No dose adjustment |

Table 5: Dose reductions in case of nephrotoxicity

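### At 3 mg/m2, and partly at 4 mg/m2, the 75% methotrexate reduction in Tables 4 and 6 cannot be given in whole 2.5 mg tablets rounded down

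*Protocol*

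**What the plan says.** Section 11.2 gives the tablet strength and the rounding rule. "The methotrexate is available in 2.5 mg tablets", and the dose is "rounded off to the nearest lower numerical which is a multiple of 2.5", so that it can be given "without the need for breaking or crushing the tablets". No exception is made for a dose lowered because of toxicity.

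The dose levels run from 15 mg/m2 down to 3 mg/m2. The concept sheet lists the lowest as "Dose Level IV: 03 mg/m"2, and Table 2 (Delivery setting) adds an optional intermediate level of 4 mg/m2 just above it.

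Section 11.4 sets the toxicity reductions as percentages that are the same at every level. Table 4 (haematological) reads "and/or Platelet < 50,000 | 75% dose" for methotrexate. The lower tier of Table 6 (hepatic) also sets methotrexate at 75%. Neither table says whether the percentage is taken of the calculated mg/m2 dose or of the tablets being taken.

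The opening of section 11.4 attaches consequences. Protocol treatment stops if an agent is held or discontinued for toxicity, and "Patients will be removed from the protocol in the event of discontinuation of any of the agents mentioned in the protocol". A reduced dose is not raised again.

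**The concern.** A percentage reduction needs enough tablets to be divisible. With one tablet there is nothing between the full dose and none, and with two the only step is a half. At the lowest levels the stated rules therefore give something other than the stated reduction, and the outcome turns on a base that the protocol does not name.

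Two staff members treating the same one-tablet patient after a neutrophil count below 1 x 10^9/L could both follow the text. One would give the full dose and the other would give none. The first outcome leaves a patient who is meant to be reduced on an unchanged dose. The second may count as holding or discontinuing methotrexate, which stops protocol treatment. In Stage 1, a stop before 2 months bears on the clinical benefit rate, one of the two endpoints that select the dose. Level 4 is a planned level, and whether a lower dose does better is the Stage 1 hypothesis.

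**Working it through.** **Inputs from the protocol.** Tablet 2.5 mg, rounded down (11.2). Levels 3, 4, 6 and up to 15 mg/m2 (Table 2). Reduction factor 0.75 (Tables 4 and 6).

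**Assumption.** The protocol gives no BSA. I use 1.2-2.2 m2 as the wide range and 1.3-1.9 m2 as the narrower one.

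**Formulas.**
- Full dose F = 2.5 x floor(level x BSA / 2.5).
- Base A, percentage of the tablets taken: R = 2.5 x floor(0.75 x F / 2.5).
- Base B, percentage of the calculated dose: R = 2.5 x floor(0.75 x level x BSA / 2.5).
- Delivered share = R / F.

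**Where the plan's 75% is approached.** At 15 mg/m2 and BSA 1.6, the calculated dose is 24 mg and F = 22.5 mg. Base A: 0.75 x 22.5 = 16.875, so 15 mg (66.7%). Base B: 0.75 x 24 = 18, so 17.5 mg (77.8%). Over BSA 1.2-2.2 the share at this level is 66.7-80%. At 6 mg/m2 and BSA 1.67-2.08, 10 mg becomes 7.5 mg, exactly 75%.

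**Level 4 (3 mg/m2).** The full dose reaches two tablets at BSA = 5/3 = 1.67.
- BSA 1.6: 4.8 mg, F = 2.5. Base A: 1.875, so 0 mg (0%). Base B: 3.6, so 2.5 mg (100%).
- BSA 1.8: 5.4 mg, F = 5. Base A: 3.75, so 2.5 mg (50%). Base B: 4.05, so 2.5 mg (50%).
- On base B the result stays at one tablet from BSA 2.5/2.25 = 1.11 to 5/2.25 = 2.22, so these outcomes hold across the assumed range.

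| Level | BSA (m2) | Full dose (mg) | Base A | Base B |
|---|---|---|---|---|
| 3 mg/m2 | 1.20-1.66 | 2.5 | 0% | 100% |
| 3 mg/m2 | 1.67-2.20 | 5 | 50% | 50% |
| 4 mg/m2 | 1.20-1.24 | 2.5 | 0% | 100% |
| 4 mg/m2 | 1.25-1.66 | 5 | 50% | 50% |
| 4 mg/m2 | 1.67-1.87 | 5 | 50% | 100% |
| 4 mg/m2 | 1.88-2.20 | 7.5 | 66.7% | 66.7% |
| 6 mg/m2 | 1.25-1.66 | 7.5 | 66.7% | 66.7% |
| 6 mg/m2 | 1.67-2.08 | 10 | 75% | 75% |
| 6 mg/m2 | 2.09-2.20 | 12.5 | 60% | 60% |

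At 6 mg/m2 a patient below 1.25 m2 takes two tablets and gets 50% (A) or 100% (B); this lies outside the narrower range. From 7 mg/m2 upward the share is 60-83.3% over the whole wide range.

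**How many Level 4 patients take one tablet.** This is P(BSA < 1.667). Under assumed distributions N(1.55, 0.15), N(1.65, 0.15) and uniform on 1.3-1.9 it is 78%, 54% and 61%. These are shares of everyone at Level 4, not of those who need a reduction.

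**The case against.** Several points on the other side are fair.

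- **The rounding rule sits in 11.2 and does not mention toxicity-reduced doses.** That is so, but it is worded for the methotrexate dose in general, and its purpose, to avoid breaking tablets, applies equally to a reduced dose. Section 11.4 gives no other way of delivering one.
- **A dose that rounds to zero is not expressly a held or discontinued dose.** This stands. That treatment stops is a possible reading of 11.4, not a stated result.
- **The affected levels may never be used, and the events may be rare there.** This also stands. The trial starts at 15 mg/m2, and only Level 4 and one optional level fail. It limits the importance, not the arithmetic.
- **The thresholds for starting a later cycle could make the tables moot.** They do not: Table 4 sets the dose for later cycles, so it still applies once counts have recovered.
- **A tablet table often sits in a dosing manual.** It may, but here two rules in the protocol itself give a wrong result when followed together.

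Two stronger readings are tempting and fail. A reader might infer that the 50% renal reduction in Table 5 is broken in the same way. It does round to 0 mg for a one-tablet patient, and it is exact for a two-tablet patient. But the same row says to avoid celecoxib, which already triggers the stopping rule of 11.4, and section 11.1 requires a clearance above 30 ml/min before each later cycle. Tablet arithmetic therefore decides nothing in that row. A reader might also infer that all of Stage 2 is exposed if a low dose is chosen. Tables 4 and 6 act only on patients who have the listed toxicity.

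**Conclusion.** The point holds in a limited form. At 3 mg/m2 no BSA from 1.2 to 2.2 m2 yields a 75% dose. The result is 0% or 100% below 1.67 m2, depending on the unstated base, and 50% above it. At 4 mg/m2 it is 50-100% over 1.3-1.9 m2. From 6 mg/m2 upward, about 60-83% is ordinary rounding.

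It affects only patients with the haematological or lower-tier hepatic toxicity at 3-4 mg/m2, in Stage 1, or in Stage 2 if such a dose is selected. The Level 4 outcomes rest on the protocol's own tablet size and rounding rule. The BSA range is assumed, and so is the share of patients on one tablet. The severity is low, but the text needs correcting because a stated reduction can come out as no change or as no drug.

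**What to change.** Reconcile section 11.2 (rounding), Table 2 (levels), the opening of section 11.4 (holding and removal) and Tables 4 and 6. State the base to which the percentage applies. Give the reduced dose in whole tablets for each tablet count at the low levels. Say what happens where no smaller tablet count exists, and whether a dose that rounds to zero counts as held or discontinued, so that a reduction never silently means unchanged or stopped. Record the tablets actually given.

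Which reduced dose or clinical rule should apply is for the investigators; none is proposed here. The cost is one short table and a sentence or two in section 11.4, with no added tests or patients.

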**Non Hematological Toxicity**

MCT has very limited non hematological side effects. The subsequent subsections show the dose modifications that should be done for derangements of metabolic parameters and non hematological toxicity during the treatment.

Nausea & Vomiting

Nausea and vomiting are unlikely. Primary prophylaxis against nausea and vomiting is not required as per the schedule mentioned in Treatment schedule above. Patients with Grade III – IV nausea and vomiting should have the dose withheld till the nausea, vomiting subsides to Grade I or less. Patients who have had one episode of Grade III / IV nausea or vomiting should have primary prophylaxis with addition of ondansetron (4 mg BD ) from the subsequent cycles of methotrexate chemotherapy. If patients continue to have Grade III- IV vomiting despite instituting antiemetic ondansetron then from the subsequent cycles of methotrexate chemotherapy additive antiemetics can be added. If in spite of high risk antiemetic prophylaxis patients continue to have vomiting ( Grade III-IV) then methotrexate should be discontinued.

Nephrotoxicity

Nephrotoxicity will be monitored in accordance with following time points

Cycle 1: Renal function test ( inclusive of serum urea, creatinine ,Na and K) for monitoring of toxicity will be done on D8 ( D7-D10)

Subsequent Cycles : Renal function test ( inclusive of serum urea, creatinine ,Na and K) for monitoring of toxicity will be done at start of each cycle.

The dose reduction in case of nephrotoxicity will be done in accordance with below mentioned table.

| Serum creatinine clearance | Methotrexate | Celecoxib  | Erlotinib          |
|----------------------------|--------------|------------|--------------------|
| > 30 ml/min                | 100 % dose   | 100 % dose | No dose adjustment |
| 15-30 ml/min               | 50% dose     | Avoid      | No dose adjustment |
| < 15 ml/min                | Avoid        | Avoid      | No dose adjustment |

Table 5: Dose reductions in case of nephrotoxicity

### Hepatic Dysfunction

Patients should be monitored for liver dysfunction prior to each chemotherapy cycle. Dose modifications will be made as per the following table.

| Bilirubin |        | ALT/AST  | Methotrexate | Celecoxib | Erlotinib |
|-----------|--------|----------|--------------|-----------|-----------|
| 2-4 x ULN | And/or | >4 x ULN | 75% dose     | 50 % dose | 50 % dose |
| >4 x ULN  | And/or | >4 x ULN | Avoid        | Avoid     | Avoid     |

Table 6: Dose adjustments to be made as per hepatic function.

The above biochemical parameters except Creatinine Clearance will be monitored prior to each cycle. Patients will have creatinine clearance measured prior to each cycle in case of any episode of Grade II renal toxicity prior to each cycle of chemotherapy.

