**Prior to subsequent cycles:**

1. Hemoglobin: > 8 g/dL
2. Total Leucocyte Count : > 2000 / cumm
3. Platelet Count : > 80,000 / cum
4. AST / ALT : < 2.5 times upper normal limit of institutional value
5. Bilirubin: Total < 1.5 times upper normal limit of institutional value
6. Calculated serum creatinine clearance above 30 ml/min
7. Resolution of other toxicities to  $\leq$  Grade I.

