## **11.3 Removal of Patients from Protocol**

Patients will be removed from Protocol treatment in the event of:

1. Inter-current illness that prevents further administration of treatment,
2. Participant unable to start any MCT cycle within 14 days of last cycle.
3. Toxicity which leads to discontinuation of one or more chemotherapy agents
4. Participant demonstrates an inability or unwillingness to comply with the oral medication regimen and/or documentation requirements
5. Participant decides to withdraw from the study
6. General or specific changes in the participant's condition render the participant unacceptable for further treatment in the opinion of the treating investigator.
7. Logistical constraints prevent from delivering chemotherapy e.g unavailability of chemotherapy medications or allergy to it.

The reason for study removal and the date the participant was removed must be documented in the study-specific case report form (CRF). Alternative care options will be discussed with the participant. In the event of unusual or life-threatening complications, participating investigators must immediately notify the Principal Investigator (or Protocol Chair)

In general, treatment interruptions should be avoided by preventive medical measures and nutritional, psychological, and emotional counseling. Treatment breaks, including indications, must be clearly documented on the treatment record.

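### Table 6 prints the same ALT/AST limit in its reduce row and its avoid-all row, so no ALT/AST value can ever lead to the reduced doses

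*Protocol*

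**What the plan says.** All places are in the Protocol.

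- **Table 6, row 1** (bilirubin, connector, ALT/AST, methotrexate): "2-4 x ULN | And/or | >4 x ULN | 75% dose". Celecoxib and erlotinib are each 50% in this row.
- **Table 6, row 2** has bilirubin above 4 x ULN, followed by "And/or | >4 x ULN | Avoid". The other two drugs are avoided as well.
- **Hepatic Dysfunction, timing:** "Patients should be monitored for liver dysfunction prior to each chemotherapy cycle".
- **Section 11.4, opening paragraph:** "If more than one dose reduction applies, then use the most stringent (i.e., the greatest dose reduction", and also "If any of the treatment agents is held or discontinued for toxicity or intolerance, further protocol directed treatment will be stopped".
- **Section 11.3** lists among the reasons for removal: "Toxicity which leads to discontinuation of one or more chemotherapy agents".
- **Section 11.4, Nephrotoxicity** introduces Table 5, which includes entries to avoid a drug, with "The dose reduction in case of nephrotoxicity will be done in accordance with below mentioned table".
- **Section 11.1**, requirement before each later cycle: "AST / ALT : < 2.5 times upper normal limit of institutional value".
- **Section 13** schedules liver function at C1D8, with tests done before that day's treatment. Table 3 gives methotrexate on D1, D8, D15 and D22.

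**The concern.** Bilirubin steps up between the two rows, from 2-4 x ULN to above 4 x ULN. ALT/AST does not. Because the connector is and/or in both rows, a single ALT/AST result above 4 x ULN calls for two different actions: continue on reduced doses of all three drugs, or give none of them. The second ends protocol treatment, so the table is meant to decide between staying on study treatment and leaving it. A two-row table with one shared limit has no graded step for transaminases, so at least one of the printed limits is evidently not the intended one.

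**Working it through.** The plan gives no numerical result to reproduce here. The check is to apply the printed rules and see which action follows.

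**1. The rows as conditions** (values in multiples of ULN, and/or read as inclusive or)

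- Row 1 (reduce): bilirubin 2-4 or ALT/AST >4.
- Row 2 (avoid): bilirubin >4 or ALT/AST >4.

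**2. The tie-break.** Section 11.4 applies the most stringent reduction. Avoiding a drug counts here, because the Nephrotoxicity text describes Table 5, including its avoid entries, as dose reduction.

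**3. Resulting action**

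| Bilirubin | ALT/AST ≤4 | ALT/AST >4 |
|---|---|---|
| <2 | no row applies | rows 1 and 2: avoid |
| 2-4 | row 1: reduce | rows 1 and 2: avoid |
| >4 | row 2: avoid | rows 1 and 2: avoid |

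Only one of the six cells ends in the 75%/50%/50% doses, and bilirubin alone puts a patient there. A grid of bilirubin 1 to 6 and ALT/AST 1 to 20 gives the same result: no reduced-dose outcome with ALT/AST above 4, and none with bilirubin below 2.

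**4. Strict-and reading.** If both conditions had to hold, bilirubin would separate the rows. An isolated ALT/AST of 20 x ULN would then trigger nothing in Table 6, and the printed connector would be contradicted.

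**5. Where a corrected band would act.** A new cycle cannot start at ALT/AST of 2.5 x ULN or more, so the practical place is an on-treatment test such as C1D8, before the D8 dose. For a patient in the new band, from D8 to the end of cycle 1 (nominal doses, before rounding down to 2.5 mg tablets):

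- Methotrexate, three doses (D8, D15, D22), 15 mg/m2 level: 3 x 15 = 45 mg/m2 now; 45 x 0.75 = 33.75 mg/m2 after correction.
- Methotrexate, 3 mg/m2 level: 3 x 3 = 9 mg/m2 now; 9 x 0.75 = 6.75 mg/m2 after correction.
- Celecoxib, 21 days (D8-D28) at 400 mg/day: 8,400 mg now; 4,200 mg after correction.
- Erlotinib, 21 days at 150 mg/day: 3,150 mg now; 1,575 mg after correction.

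Above 4 x ULN the action is to avoid all three drugs, both before and after the correction.

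**The case against.** The best defence is that the rule as printed still gives one answer. The most-stringent clause sends every overlap to the safer action, and the cycle-start requirement already keeps most patients with raised transaminases off treatment. The Hepatic Dysfunction text ties monitoring to cycle starts, so using Table 6 at C1D8 is an inference from the study calendar and the general toxicity rule. All of this stands, and it limits the practical reach. It does not repair the table: the ALT/AST entry in row 1 can never set a dose, and a cycle-start requirement prescribes no reduced dose.

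Three stronger readings are tempting, and the documents do not support them.

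- *Patients above 4 x ULN wrongly lose treatment.* This assumes that row 1 was meant to govern them. The Protocol does not say so, and under the correction proposed here they still receive none of the three drugs.
- *The lack of any adjustment between 2.5 and 4 x ULN is itself an error.* Cycle-start limits stricter than dose-modification limits are usual in this Protocol. Platelets must exceed 80,000 to start a later cycle, but methotrexate is reduced only below 50,000. Bilirubin must be below 1.5 x ULN to start, but Table 6 begins at 2 x ULN. The gap therefore neither proves an error nor fixes 2.5 as the intended lower limit.
- *No ALT/AST value leads to any dose reduction.* The tie-break works only if avoiding a drug counts as a reduction. The accurate statement is that no ALT/AST value leads to the 75%/50%/50% row.

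**Conclusion.** The point holds as a minor error in an operative dosing table. It rests on the printed connector read as inclusive or and on the most-stringent rule covering avoidance. Without that rule, the same laboratory value would carry two conflicting instructions, which is no better. The table appears complete in the extracted text, though the original page could not be seen.

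The size is limited to patients whose ALT/AST falls in the corrected band at an on-treatment test. For them, methotrexate, celecoxib and erlotinib for the rest of the cycle would fall by 25%, 50% and 50%. The Protocol gives no frequency of such values, so no patient count is offered. A reader might infer bias in the stage 1 dose decision or in stage 2 PFS, but nothing in the document supports such a claim.

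**What to change.** In Table 6, replace the row 1 ALT/AST cell with a band that ends at 4 x ULN and leave values above 4 x ULN in the avoid row. The two rows then no longer overlap on ALT/AST. Where bilirubin and ALT/AST point to different rows, the most-stringent rule still decides.

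The investigators should set and confirm the lower limit. One candidate is 2.5 x ULN, the section 11.1 cycle-start limit. It should first be checked against the section 11.4 rule that Grade I toxicity does not change the dose.

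The cost is one table cell and a confirmation from the investigators. The downside is a somewhat lower dose in the few patients who fall in the new band.
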